##### Kubios Software: Heart Rate Variability

Kubios software will be used to evaluate heart rate variability (HRV). HRV is a recognized indicator for assessing the activity of the autonomic nervous system (ANS) in the regulation of cardiovascular function and its adaptive response to various stimuli [69]. HRV has been shown to be a reliable measure (ICC 0.78–0.90) for evaluating cardiovascular performance and autonomic function in athletes [70]. In the current study, HRV recording will be carried out using a Polar H10 telemetric heart rate monitor (Polar Electro Oy, Kempele, Finland). Data analysis will be performed with the Kubios HRV software (version 1.8.14; Kubios Oy, Kuopio, Finland). HRV will be determined via an incremental graded exercise test (GXT), which progressively increased treadmill velocity until volitional exhaustion. The GXT will begin at 8 km·h^−1^, with velocity increments of 1 km·h^−1^ per minute until volitional exhaustion, maintaining a 0% treadmill gradient. Heart rate (HR) will be recorded across three distinct phases: pre-exercise (resting phase), during exercise, and post-exercise (recovery phase).

Prior to commencing the test, resting heart rate variability (HRV) will be recorded for five minutes in a supine position. The examiners will ask the athletes not to talk or move during the recording of heart rate variability. All athletes will follow a standardized 10 min warm-up protocol, consisting of 5 min of aerobic exercise and 5 min of stretching, primarily targeting the muscles of the lower limbs. Subsequently, they will undergo a graded treadmill exercise test, commencing at a speed of 8 km·h^−1^, with incremental increases of 1 km·h^−1^ per minute until volitional exhaustion is reached. Immediately after test completion, participants will be placed in supine position, remaining still and refraining from speaking again, and the examiners will record the HRV of recovery for 15 min. Recovery HRV will then be recorded in three phases: 0–5 min, 5–10 min, and 10–15 min. Blood lactic acid will be recorded before and after exercise, and all athletes must have a level ≥ 2 mmol/L before starting the test.

For the assessment of HRV, time-domain indices will be used, including the interval between two successive heartbeats (RR interval), the number of heartbeats per unit of time (HR), the standard deviation of normal-to-normal intervals (SDNN), and the root mean square of successive differences between adjacent intervals (RMSSD). In addition, frequency-domain measures will be analyzed, including the absolute power of heart rate variability in the low-frequency band (LF: 0.04–0.15 Hz) and the high-frequency band (HF: 0.15–0.40 Hz), the ratio of low- to high-frequency power (LF/HF), and total power (TP) [71,72]. For the statistical analysis, mean values of RR intervals (s), mean heart rate (HR; bpm), SDNN (ms), RMSSD (ms), LF (ms^2^), HF (ms^2^), LF/HF ratio (%), and total power (TP; ms^2^) will be used, as recorded during the resting phase and across the three phases of the recovery phase.

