## Abstract

**Background/Objectives:** This study aims to evaluate the effectiveness of binaural beats (BB) on the autonomic nervous system (ANS), kinesiophobia of reinjury and fitness biomarkers in professional athletes with chronic musculoskeletal injuries. **Methods**: A total of 54 athletes aged 18–25 years, engaged in open-skill sports and experiencing chronic lower-limb injuries for over three months, will be recruited. They will be randomly assigned to one of three groups: an intervention group, a placebo group, and a control group. All athletes will undergo a 15 min auditory intervention five times per week for four weeks. The intervention group will listen to BB embedded in music at high beta and gamma frequencies (30–100 Hz) with guided instructions. The placebo group will receive placebo BB within the same music framework, while the control group will listen only to the music background. Assessments will be conducted at baseline, immediately post-intervention, and at a 4-week follow-up. The primary outcomes will be kinesiophobia of reinjury, ANS function, and heart rate variability (HRV), assessed using the Tampa Scale of Kinesiophobia (TSK-17), Sympathetic Skin Response (SSR), and HRV analysis, respectively. Secondary outcomes will include sport-related anxiety and pain beliefs, assessed using the Sport Competition Anxiety Test (SCAT-15) and the Pain Beliefs and Perceptions Inventory (PBPI-16), respectively; handgrip strength, assessed using the Hand Grip Test; and fitness-related biomarkers, including maximal oxygen uptake (VO_2_max) and blood lactate concentration. **Conclusions**: These findings may provide evidence supporting BB as a complementary, non-invasive intervention to enhance psychological and physiological rehabilitation in injured athletes. Ethics and Dissemination: The study has received ethical approval and is registered on ClinicalTrials.gov. Findings will be disseminated through peer-reviewed publications, conferences, and academic presentations.

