##### Maximal Oxygen Uptake and Lactate Levels

The ergospirometry test will be conducted on a treadmill following the protocol described by Bielik et al. [66]. Respiratory variables will be recorded using a breath-by-breath gas analyzer (K5, Cosmed, Rome, Italy), calibrated prior to each session according to the manufacturer’s instructions. Maximal oxygen uptake (VO_2_max) will be evaluated as an objective measure of aerobic capacity and as a robust indicator of cardiorespiratory function [67]. VO_2_max will be determined via an incremental graded exercise test (GXT), which progressively increases treadmill velocity until volitional exhaustion, with estimated time of at least 12–20 min [68].

Before the start of the test, the researchers will record HR and blood pressure in a resting state. Athletes will be placed in a supine, relaxed position and instructed to remain still and refrain from speaking for 5 min. Prior to starting the test, all athletes will perform a standardized warm-up comprising 5 min of cycling on a cycle ergometer followed by 5 min of dynamic lower-limb stretching.

The blood lactate concentrations (La) will be measured in two phases before and at the end of the ergospirometry test and the results (mmol) will be used for statistical analysis.

The GXT will begin at 8 km·h^−1^, with velocity increments of 1 km·h^−1^ per minute until volitional exhaustion, maintaining a 0% treadmill gradient. Termination criteria will include (a) a plateau or decline in VO_2_ despite increasing workload, accompanied by a respiratory exchange ratio ≥ 1.10, (b) the ratio VE/VO2 ≥ 30, (c) the ratings of perceived exertion (RPE) 18–20 of borg scale and (d) the concentration of lactic acid in blood ≥ 9 mmol/L [67]. Athletes will receive verbal encouragement, primarily during the final minute. Respiratory variables will be continuously recorded using a breath-by-breath gas analyzer, which will be calibrated prior to each session according to the manufacturer’s instructions. VO_2_ values will be averaged over the final 10 s of each 1 min stage. All procedures will be supervised by two exercise physiologists to ensure participant safety and protocol fidelity. The results of oxygen uptake relative to body mass (VO_2_/kg), the metabolic equivalents (METs) and the ratio of carbon dioxide production to oxygen consumption (VCO_2_/VO_2_), which is defined as respiratory quotient (RQ), will be used for statistical analysis.

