However, limited evidence exists regarding the effects of BB in professional athletes with chronic lower-limb MSK-I, particularly with respect to kinesiophobia, autonomic function, handgrip strength, HRV, and fitness-related biomarkers. The present study therefore aims to address this gap by investigating whether a music-based binaural beats intervention can influence psychological and physiological outcomes relevant to fear of reinjury. It is hypothesized that reductions in kinesiophobia, competitive anxiety, and maladaptive pain beliefs will be accompanied by improvements in ANS function, as reflected by SSR parameters (latency and amplitude) and HRV following BB stimulation. Improvements in autonomic regulation may subsequently enhance cardiovascular recovery, exercise tolerance, handgrip strength, and aerobic fitness biomarkers, thereby contributing to a safer and more confident RTS process.

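### HRV is a primary outcome, but the pre-exercise resting recording has no priority over three post-exhaustion windows, the first of which gives SDNN and total power that mainly track the falling heart rate unless a smooth trend is removed

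*Protocol article*

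**What the plan says.** The Abstract states: "The primary outcomes will be kinesiophobia of reinjury, ANS function, and heart rate variability (HRV"), together with the instruments used. It names no HRV index or window.

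The section Kubios Software: Heart Rate Variability (within 2.3.6) describes the source: "HRV will be determined via an incremental graded exercise test (GXT), which progressively increased treadmill velocity until volitional exhaustion". The recordings are:

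- Before the test: "Prior to commencing the test, resting heart rate variability (HRV) will be recorded for five minutes in a supine position".
- After the test: "Immediately after test completion, participants will be placed in supine position, remaining still and refraining from speaking again". Then: "Recovery HRV will then be recorded in three phases: 0–5 min, 5–10 min, and 10–15 min".

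Eight indices go to analysis: mean RR, mean HR, SDNN, RMSSD, LF, HF, LF/HF and total power, "as recorded during the resting phase and across the three phases of the recovery phase".

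The test has no fixed end load. It runs "with velocity increments of 1 km·h^−1^ per minute until volitional exhaustion, maintaining a 0% treadmill gradient". The Discussion expects the intervention to act on this: "Improvements in autonomic regulation may subsequently enhance cardiovascular recovery, exercise tolerance". Section 2.5 provides for adjusted analyses only where baseline imbalance is found.

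**The concern.** The four windows do not measure the same thing. The resting recording is taken supine before any exercise at that visit. The recovery recordings begin at exhaustion, which raises two problems.

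1. **Trend.** SDNN and total power summarise variation around a mean. When the mean itself falls quickly, as in the first minutes after exhaustion, most of what they register is the size of the fall.
2. **Load.** The preceding exercise ends when the athlete stops. If the intervention changes how far athletes run, the arms enter recovery from different loads after randomisation.

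With no order of priority, a primary HRV result could be claimed from, or contradicted by, a recovery window whose values shifted with no change in beat-to-beat variability. The recording that avoids both problems is already planned but carries no more weight than the others.

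**Working it through.** The plan gives no figure to reproduce here. The checks are a count, a simple model and a comparison of the relevant sections.

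**1. Count.** 8 indices × 4 windows = 32 HRV values per visit. Recovery gives 8 × 3 = 24, and 24/32 = 75%. All 24 follow the unfixed load, but they are not equally exposed to the trend. For mean HR and mean RR, the fall is the recovery signal itself.

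**2. Heart-rate fall alone.** The model is HR(t) = plateau + (peak − plateau) × exp(−t/τ) and RR = 60,000/HR(t) ms, with beats laid end to end and no beat-to-beat variability. SDNN is the standard deviation of RR in each window; RMSSD is the root mean square of successive RR differences. The inputs are assumptions, not in the documents: peak 180 or 190 bpm, plateau 100 or 115 bpm, τ 60, 90 or 150 s.

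| Window | SDNN from the fall alone (ms) |
|---|---|
| 0–5 min | 45.0–86.7 |
| 5–10 min | 0.5–15.9 |
| 10–15 min | 0–2.4 |

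RMSSD in the first window is 0.22–0.57 ms. For scale, a fall from 190 towards 100 bpm moves RR from 60,000/190 = 316 ms towards 60,000/100 = 600 ms.

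**3. Share of the total when real variability is present.** Assumed: 188 falling to 98 bpm, τ 60–150 s, beat-to-beat SD 3–20 ms, no detrending.

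| Window | Share of SDNN variance | Share of total power |
|---|---|---|
| 0–5 min | 91–100% | 95–100% |
| 5–10 min | 0–95% | 0–97% |
| 10–15 min | usually 0–5%, up to 39% | usually 0–11%, up to 60% |

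The upper values in the last row arise only with the slowest decay and the least variability. The fall's share of squared RMSSD is at most about 2% in every window.

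**4. Detrending.** In the model of step 2, a straight-line detrend of the first window leaves an SDNN of 7–33 ms. A smoothness-priors detrend reduces it to about 0.1 ms or less.

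**5. Direction.** In the same model, raising the peak from 180 to 190 bpm raises first-window SDNN in all six settings, for example from about 80 to 87 ms (plateau 100, τ 60). Raising the plateau from 100 to 115 bpm lowers it, for example from about 80 to 55 ms (peak 180, τ 60). In a separate run with real variability held constant, a plateau 5 bpm higher moved first-window SDNN from 86.1 to 77.4 ms while RMSSD stayed near 14 ms. SDNN can therefore move either way with unchanged variability.

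**6. Can load differ by arm?** Section 2.4 gives the verbal guidance to both the intervention and placebo groups, so guidance can change effort only relative to the music-only control. For intervention against placebo, what remains is the Discussion's expectation of better exercise tolerance, and the statement in Section 2.4 that the beat frequencies are meant to improve confidence and performance.

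**The case against.** The strongest reply has four parts.

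- **Resting HRV is recorded and analysed.** This stands. A reader might infer that autonomic change cannot be separated from test effort anywhere in this trial. The documents do not support that, because the resting recording precedes the test. The defect is missing priority.
- **The artefact depends on processing that an article need not describe.** This stands in part. A smooth detrend would remove it, and its absence from the article is no fault. Detrending would not remove the dependence on load, and the equal standing of the windows is what the article itself states.
- **Effort is measured.** Section 2.3.6 uses respiratory exchange ratio, VE/VO2, perceived exertion and lactate as termination criteria, and analyses respiratory quotient and lactate. This allows effort to be examined, but no stated HRV analysis uses these markers.
- **Recovery HRV is a legitimate measure of autonomic reactivation, and the Discussion has exercise tolerance improving through autonomic regulation.** This stands as a reason to keep the windows, read against the load that preceded them.

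Two further inferences are tempting. One is that a beneficial effect on effort would show up as poorer recovery HRV; step 5 shows that the sign depends on the assumptions. The other is that LF and LF/HF are equally spoiled. Trend-only LF power in the first window is about 75–258 ms² with neither taper nor detrending, but at most about 3 ms² with linear detrending, so that cannot be said from this document.

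**Conclusion.** The point holds in a limited form. HRV is a primary outcome, 24 of its 32 values per visit come after exhaustion, and the resting recording has no priority. Without removal of a smooth trend, SDNN and total power at 0–5 minutes mainly describe the heart-rate decline. At 5–10 minutes the size of the problem depends on the assumed decay, and at 10–15 minutes it is usually small. RMSSD is nearly immune to the trend, though effort may still affect it physiologically.

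Separately, all recovery values follow a load that is not fixed and that the intervention is hypothesised to change. This makes them harder to read as autonomic change than the resting values, in a direction that is not known. The numerical sizes rest on assumed heart-rate curves; the lack of priority rests on the text alone. This should be changed before analysis, but it does not invalidate HRV as an outcome.

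**What to change.** - In the Abstract and the HRV section, name the 5-minute supine pre-exercise recording, with log RMSSD as the index, as the primary HRV measure. Make recovery HRV secondary or exploratory.
- For 0–5 minutes, report heart-rate recovery (end-test HR minus HR at a fixed minute), and do not interpret SDNN or total power as autonomic variability.
- Present the 5–10 and 10–15 minute windows descriptively, alongside end-test speed and the recorded effort markers. Do not offer a treatment effect adjusted for end-test speed: it is measured after randomisation, and conditioning on it could itself bias the group comparison.

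The cost is wording, since every HRV recording is already planned. The downside is that recovery HRV can no longer support a primary claim.

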### 2.4. Intervention: The Binaural Beats Intervention Program

BB is delivered through an auditory stimulus waveform that is interpreted as a brainwave pattern by the Reticular Activating System (RAS). The RAS regulates arousal, kinesiophobia, attention, and awareness—key elements of consciousness itself [73,74]. In this study, BB is layered with background music and will be provided in MP3 format following specific guidance, in the English language, based on fearless motion. All stimuli will be presented binaurally at High Beta and Gamma frequencies, via an auditory system incorporating headphones [75]. In fact, the purpose of High Beta and Gamma frequencies on athletes is to improve the athlete’s psychomotor and self-regulation ability, their confidence, and subsequent performance in important competitions [76]. The Binaural Beats (BB) intervention program will be designed and produced by the Monroe Institute (Faber, VA, USA).

This BB music-based intervention will be received in high beta and gamma frequencies (30–100 Hertz) at 30 bpm (slow tempo), 60 bpm (normal tempo), and 100 bpm (fast tempo). The binaural beat stimuli will consist of mixed sinusoidal tones producing frequency patterns will crop in length to a duration of six times intervals (total 15 min): 0–2 min the slow tempo (Grounding), 3 min (2–5 min) the slow tempo (Relaxation/Intention Setting), 3 min (5–8 min) the normal tempo (Imagery Begins), 2.5 min (8–10.5 min) normal tempo (Emotional Processing + Imagery/Movement), 2.5 min (10.5–13 min) fast tempo (Active Visualization + Affirmation), and 2 min (13–16 min) fast tempo (Return to Awareness, Light Activation) enabling athletes to hear the music; this duration will also be likely to yield more pronounced emotional response [77].

The intensity will be modified at approximately the isochrone tones to 14–16 dB.

Each athlete will receive the musical intervention via the website binaukine.com, which has been specifically designed by the researchers exclusively for the purposes of the present study. Furthermore, participants’ compliance with the study protocol will be monitored by the researchers through the frequency of the athletes’ visits to the website.

The BB music-based intervention will be performed prior to each training session or competition, as part of the athletes’ warm-up routine. Athletes will be instructed to conduct the listening sessions in a quiet environment, seated comfortably with their eyes closed, and to avoid distractions from external stimuli during the intervention. All groups will receive the BB music-based interventions for 20 sessions, lasting 15 min per session, 5 times per week, over a period of 4 weeks.

Before beginning the BB music-based intervention phase, all athletes will attend a familiarization session during which the researchers will provide detailed instructions on how to perform the intervention. During the main intervention phase, the first session will be supervised by the research team, while the remaining sessions will be carried out individually, at different times according to each athlete’s training schedule. Each group will randomly receive the BB music-based intervention program.

The intervention group will receive a complete BB music-based intervention program. The placebo group will receive the same music-based intervention program with the verbal guidance but without the binaural beats. The control group will listen only to the music track, with the same music background as the intervention and placebo groups.

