Binaural beats (BB) are an auditory phenomenon often layered with background music and referred to as binaural music. BB occurs when two tones of slightly different frequencies are presented separately to each ear. The brain then perceives a third tone, known as a binaural beat, which equals the difference between the two frequencies. For instance, if one ear hears a tone at 300 Hz and the other at 306 Hz, the brain detects a binaural beat of 6 Hz [41]. Binaural beats require the use of headphones so that each frequency reaches only one ear. The sound of binaural beats is created by the brain rather than by the physical mixing of sound waves in the air; they are perceived binaurally and are often experienced as stronger, associated with the induction of specific brainwave states [41]. BB have gained attention for their potential psychological and physiological effects, particularly in stress modulation and attentional control by using different frequencies (such as delta, theta, beta, alpha and gamma waves). In athletic contexts, binaural beats have been suggested to reduce pre-competition anxiety and enhance concentration, which may be especially beneficial during rehabilitation and RTS [42,43,44]. Physiologically, binaural beats appear to influence ANS activity by modulating sympathetic–parasympathetic balance. Listening to theta-frequency binaural beats post-exercise has been shown to increase HRV, indicating enhanced parasympathetic activation and relaxation [45]. Similar findings have been reported in stress-recovery contexts among military personnel [46]. Evidence examining the effects of binaural beats on kinesiophobia, ANS activity, reinjury anxiety, pain beliefs, and fitness biomarkers in athletes with chronic musculoskeletal injuries remains limited.

Binaural beats constitute a non-invasive form of auditory stimulation that may modulate athletes’ psychophysiological state by influencing cortical oscillatory activity, arousal regulation, and ANS function [41,44,45]. This mechanism is particularly relevant to kinesiophobia, which extends beyond maladaptive beliefs to encompass anxiety, heightened threat perception, increased physiological arousal, and ANS dysregulation. Consequently, binaural beats may reduce fear-related responses by promoting autonomic balance, enhancing psychological readiness, and supporting confident movement.

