### 2.2. Procedures

This double-blind randomized controlled trial will investigate the effects of binaural beats on biopsychological outcomes in professional athletes with a history of chronic lower-limb musculoskeletal injuries. The study will be conducted in three phases: baseline (pre-intervention), immediately after the four-week intervention, and four weeks after completion of the intervention. Outcome measures will include self-report questionnaires assessing kinesiophobia, sport-related anxiety, and pain beliefs; physiological assessments of autonomic nervous system (ANS) function; handgrip strength; and fitness-related biomarkers, including maximal oxygen uptake (VO_2_max), blood lactate concentration, and heart rate variability (HRV). All athletes will complete a four-week standardized binaural beats music-based intervention incorporated into the warm-up phase prior to each training session and official game. The BB intervention will be administered 5 times per week (pre-training and pre-game), resulting in a total of 20 sessions. Each session will consist of 15 min of music listening (Figure 1).

Prior to initiating the intervention, athletes will receive detailed oral and written information regarding the study aims and assessment procedures from licensed physiotherapists with five years of clinical research experience. Data collection will include both subjective and objective measures and will be conducted at three time points: baseline (pre-intervention), immediately post-intervention, and four weeks after the completion of the intervention. Written informed consent will be obtained from all participants before enrollment.

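### The placebo track is described inconsistently, and the text does not settle whether it keeps the tones that carry the beat; if it does not, experimental versus placebo confounds the beat with audible tones

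*Protocol article*

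**What the plan says.** The protocol article describes the arms in several places.

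- **Abstract, intervention arm:** "The intervention group will listen to BB embedded in music at high beta and gamma frequencies (30–100 Hz) with guided instructions".
- **Abstract, other arms:** "The placebo group will receive placebo BB within the same music framework, while the control group will listen only to the music background". The placebo form of the beats is not defined, and guidance is not mentioned for this arm.
- **Section 2.4, placebo arm:** "The placebo group will receive the same music-based intervention program with the verbal guidance but without the binaural beats".
- **Section 2.4, control arm:** "The control group will listen only to the music track, with the same music background as the intervention and placebo groups".
- **Section 2.2:** "All athletes will complete a four-week standardized binaural beats music-based intervention". Section 2.4 has a similar sentence giving the programme to all groups. It also says that every stimulus is presented at high beta and gamma frequencies, with no arm excepted.

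On the stimulus itself, the Introduction explains that "BB occurs when two tones of slightly different frequencies are presented separately to each ear". Section 2.4 adds that "The binaural beat stimuli will consist of mixed sinusoidal tones producing frequency patterns" and that this material is layered with the background music.

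Two claims rest on this comparator. Section 2.1 says that participants stay blinded to allocation. Section 5 says that having three arms lets the effect of the beats be examined over and above music and spoken guidance.

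**The concern.** A binaural beat is not a sound on the recording. By the Introduction's account the brain produces it from two real tones, one in each ear. A placebo without beats can therefore be made in two ways: remove the whole tone layer, or keep the tones and send the same frequency to both ears. The first removes an audible component as well as the beat. The second removes only the beat.

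Section 2.4 describes a layered product and then the same product minus the beats. The natural reading is that the layer is left out, but the text does not say so. On that reading, a difference between the experimental and placebo arms could come from listening to sustained tones under the music, with no contribution from the beat. The two tracks would also sound different. TSK-17, a primary outcome, is self-reported and so is exposed to any loss of blinding.

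**Working it through.** The document gives no figure to reproduce on this point. The check sets the descriptions side by side and asks what each pairwise contrast would vary.

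**Components.** M = music, G = spoken guidance, T = sinusoidal tones, B = frequency difference between the ears (the beat). B cannot exist without T, but T can exist without B.

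| Reading | Experimental | Placebo | Control | Experimental − placebo |
|---|---|---|---|---|
| 2.4, tone layer left out | M+G+T+B | M+G | M | T+B |
| 2.4, same tone to both ears | M+G+T+B | M+G+T | M | B |
| Abstract taken literally, matched-tone sham, no guidance | M+G+T+B | M+T | M | G+B |
| 2.2 taken literally, beats for all | includes B | includes B | includes B | B cancels |

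**Step 1: which contrast carries the claim.** Under 2.4, experimental minus control always contains G, so it cannot credit an effect to the beat. Experimental minus placebo is the only contrast that holds M and G constant.

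**Step 2: whether analysis could rescue it.** In the first row, code the arms in the order experimental, placebo, control. Then T = (1, 0, 0) and B = (1, 0, 0). The two indicators are identical, so no model, covariate adjustment or post hoc test on these three arms can separate tone from beat. In the second row T = (1, 1, 0) and B = (1, 0, 0), and experimental minus placebo estimates B alone.

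**Step 3: extent.** Athletes in the contrast: 18 + 18 = 36. Planned exposure per athlete: 20 sessions × 15 min = 300 min. Any mismatch between the tracks would be present in every session.

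**Step 4: what cannot be computed.** The document gives no estimate of the effect of tones alone on any outcome and no rate at which athletes might guess their arm. The bias therefore has neither a sign nor a size that can be derived.

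**The case against.** Several objections have weight.

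- **The tones are not stated to be dropped.** Since the beat is a percept, the same tone in both ears also meets the wording of 2.4. A reader might infer that the arms are known to differ in audible tones. The document does not support that; it leaves the matter open. This objection stands, and the consequence is conditional.
- **The definitions may not be incompatible.** The Abstract's undefined term can be read as shorthand for the 2.4 track, and its silence on guidance may be the brevity of a summary. This stands too: the descriptions are inconsistent, but no outright contradiction is proved between these two places.
- **The sentences about all athletes and all groups mainly set the schedule,** and 2.4 then gives each arm its content. They are probably loose wording. Read literally, they still conflict with a placebo without beats and a music-only control, so they need correcting.
- **Section 5 promises only a comparison beyond music and guidance,** and 2.4 holds both constant. That is fair. However, it credits the effect to the beats themselves, which a tone-free placebo could not support.
- **An article may leave audio specification to a fuller protocol.** Silence on tones alone would not be a finding. Here the article states what the placebo contains, varies that statement between sections, and rests an inference and a blinding claim on it.

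Two further inferences are tempting and unsupported. Section 2.4 mentions isochrone tones in an unclear sentence that assigns them to no arm, so they cannot be counted as another difference between the tracks. Nothing in the document shows that athletes will compare tracks; after the first session, listening is individual and at different times.

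**Conclusion.** The point holds in conditional form. The placebo is described inconsistently across the Abstract, 2.2 and 2.4, and the text does not fix whether its track keeps the tones. If the tone layer is left out, the trial's key contrast tests tones and beat together, an effect could not be attributed to the beat, and participant blinding may be weakened. If the tones are already matched, the contrast is sound and one clarifying sentence settles the matter.

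The conclusion rests on the Introduction's definition of a beat and on 2.4's description of the stimulus as tones layered with music. It depends on no assumption about effect size, power or correlation. It should be resolved before the tracks are used, because a mismatch built into the audio cannot be removed in the analysis.

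**What to change.** Use one definition of the placebo in the Abstract, 2.2 and 2.4: the same music, guidance, timing, loudness and sinusoidal tones as the active track, with the same tone frequency sent to both ears, so that the difference between ears is zero and no beat arises. In addition:

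- State that any isochrone component is in both of these tracks or in neither.
- Reword the sentences that give the binaural-beat programme to all athletes or groups, so that they refer to the assigned audio track, and limit the sentence on stimulus frequencies to the arm it describes.
- If a tone-free placebo is kept, limit the claim in Section 5 to the effect of the tone-plus-beat layer.

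The cost is one audio track to specify or re-render, plus text edits. Section 2.4 says the programme is still to be designed and produced, and no extra athletes or visits are needed. The trade-off is that tone exposure itself is not tested, and placebo versus control then varies guidance and tones together (M+G+T against M). The stated hypotheses concern the beats, so little of what the trial asks is lost.
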